### Statistical analyses

The primary analysis will be performed as an intention-to-treat, ITT, analysis.

A regression model for count data with “zero inflation”, i.e. with a large proportion of cases without incapacity to work, is used to analyze the primary outcome. For this purpose, the zip command in the statistical package STATA is used. The statistical analyses of the other outcome variables are performed with generalized linear mixed-effects models [24].

These models are appropriate for the analysis of cross-sectional and longitudinal data on primary and secondary outcomes, which may be continuous (cost, quality of life) or categorical (early retirement) variables. Interdependencies between measurements in longitudinal data can be appropriately handled by including mixed effects. The application of the regression models to variables with different scale levels is made possible by the appropriate choice of the link function (e.g. identity for continuous variables, logistic for dichotomous variables) and the error distribution (e.g. normal distribution for continuous target variables, binomial distribution for dichotomous variables).

For data analysis with generalized linear mixed models, corresponding procedures are available in all relevant statistical packages (e.g. SPSS, SAS, Stata, R). Beyond these advantages of the chosen analysis model, it should be emphasized that with these models it is possible to specify and statistically test relevant hypotheses about the group, time, period, and interaction effects. These models also allow the handling of missing follow-up data.

For the analysis of cost data, special gamma regression models can be used according to the distributional properties of the dependent variable. With the help of suitable methods, the dispersion of costs and efficiencies is explained, i.e., those parameters are determined which have a significant influence on the costs and efficiencies of the measures.

Cost-benefit analysis: Based on the intervention costs and the saved costs (if applicable), the profitability of the measures is determined. In addition, the difference between intervention costs and the potentially saved costs for MS patients is compared to the effectiveness of the measures (cost-effectiveness analysis), to give information on the intervention’s advantageousness compared to other health policy instruments.

Institutional conditions: Based on the survey of the intervention costs and the acceptance of the intervention by the health care providers, the conditions for a successful implementation of the intervention as part of the standard care are elaborated and evaluated.

An interim analysis is not planned.

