### Sample size

The calculation of sample size was done for the analysis of the primary outcome “number of sick leave days” per patient within 12 months. The calculation assumes that the difference in sick leave days is to be an average of 5 days (or 20% of the average sick leave days for MS patients in Germany) between the intervention and the control group. This number is deduced from the German statistics on types of illness [5], with an annual average number of 25 days of incapacity to work due to MS among the statutorily insured persons. Further, based on a database analysis of the insurances taking part, up to 50% of the insured persons with MS do not have any days of incapacity to work in a 12-month observation period. Hence, the number of cases is calculated with a regression model for count data with “zero inflation”.

Depending on the assumption about the proportion of insured persons without sick leave days (30% vs. 50%), with a statistical power of 80%, and a 2-sided significance level of 0.05, the minimum sample size necessary to identify a group difference for the primary outcome of sick leave days is between 600 and 860. An expected drop-out of 20% in the course of the twelve-month comparison period leads to an increase in the net case numbers to the gross case numbers of *N* = 750 and *N* = 1075 (Table 1).

**Table 1 Tab1:** Results of the calculations for determining sample size

Patients without days of incapacity to work within 12 months (in %)	Net number of cases	Gross number of cases^a^
30% 50%	600 860	750 1.075

^a^Drop out of 20% in 12 months

Therefore, we aim for an initial gross sample size of 950 cases in total (475 cases per group). This number of cases is somewhat closer to the upper limit and would thus make it possible to achieve the planned power even if the actual conditions deviate from the assumptions made.

The strategies to achieve adequate recruitment to reach the target sample size had been.

based on the number of patients being treated in the past in the neurological practices who would have fulfilled the eligibility criteria. Neurological practices will be identified with the help of the BDN, the Professional Association of Neurologists.

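### The primary analysis names zero-inflated Poisson (Stata zip) with no allowance for overdispersion; with default standard errors, even mild overdispersion in sick leave days takes type I error from 5% to about 19-29%

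*Protocol article*

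**What the plan says.** The Statistical analyses section of the protocol article sets the model for the primary outcome: "A regression model for count data with “zero inflation”, i.e. with a large proportion of cases without incapacity to work, is used". The next sentence fixes the software call: "For this purpose, the zip command in the statistical package STATA is used". For this outcome the article mentions no negative binomial part, no check for overdispersion and no robust variance. The same section does fit the distribution to the data for costs, where it offers gamma models. Its mixed models are for the other outcomes.

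The Sample size section uses the same model class: "the number of cases is calculated with a regression model for count data" with zero inflation. Its inputs are a mean of 25 days, a target where "the difference in sick leave days is to be an average of 5 days" (20%), a zero share of 30% or 50%, 80% power and a two-sided level of 0.05. The net totals are 600 and 860, or 750 and 1,075 after 20% drop-out, and the target is 950. No standard deviation, dispersion or tested coefficient is given.

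**The concern.** Stata's zip is zero-inflated Poisson. It mixes a group that always has zero days with a Poisson count for everyone else. The mixture explains why many patients have no leave. It does not explain why those with leave differ so much from one another, because the Poisson part ties their variance to their mean. With a mean of 36 to 50 days among patients with leave, the model assumes an SD of about 6 to 7 days; with a mean of 25, it assumes 5 days. Sick leave comes in spells, so the days are not independent events and a wider spread is to be expected.

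If the spread is wider, the default standard error of the treatment coefficient is too small. The trial could then declare a benefit or a harm for an intervention that changes nothing. This affects the p-value and the confidence interval of the primary outcome.

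**Working it through.** **Inputs.** From the Sample size section: mean 25 against 20 days (rate ratio 0.8), zero share π = 0.30 or 0.50, net N 600 or 860, 950 gross. From the Statistical analyses section: zip. Analysed per arm: 475 × 0.8 = 380. Constants: (1.960 + 0.842)² = 7.849 and ln(0.8)² = 0.04979. The dispersion α (variance = m + αm²) is not in the article and is varied below.

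The article does not say whether 25 and 20 are means over all patients or over those with leave, so both readings are carried. The first gives means among patients with leave of 35.7/28.6 (π = 0.30) or 50/40 (π = 0.50). The second gives 25/20.

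**1. The plan's own figures.** The drop-out step reproduces: 600/0.8 = 750 and 860/0.8 = 1,075.

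For a plain zip count-part test, total N = 2 × 7.849 × (1/m₁ + 1/m₂) / [(1 − π) × 0.04979]:

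| π | m₁/m₂ | 1/m₁ + 1/m₂ | Total N | Stated |
|---|---|---|---|---|
| 0.30 | 35.7/28.6 | 0.063 | 28 | 600 |
| 0.50 | 50/40 | 0.045 | 28 | 860 |
| 0.30 | 25/20 | 0.090 | 41 | 600 |
| 0.50 | 25/20 | 0.090 | 57 | 860 |

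The stated totals therefore do not come from a plain zip test of a 20% reduction in the count part.

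**2. Dispersion implied if the count part was sized.** The stated totals contain 600 × 0.7 = 420 and 860 × 0.5 = 430 patients with leave, which is nearly the same number. Solve 7.849 × (2α + 1/m₁ + 1/m₂)/n = 0.04979, with n = 210 or 215 patients with leave per arm:

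- π = 0.30: 210 × 0.04979/7.849 = 1.332, so α = (1.332 − 0.063)/2 = 0.63, or (1.332 − 0.090)/2 = 0.62.
- π = 0.50: 215 × 0.04979/7.849 = 1.364, so α = (1.364 − 0.045)/2 = 0.66, or (1.364 − 0.090)/2 = 0.64.

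The variance 1 + αm₁ is then about 17 to 34 times the mean. The true standard error exceeds the zip default by √(1.332/0.063) = 4.6 or √(1.332/0.090) = 3.8 at 30% zeros, and by √(1.364/0.045) = 5.5 or √(1.364/0.090) = 3.9 at 50%.

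**3. Type I error.** With no treatment effect the standard error is too small by about f = √(1 + αm), and the error rate is 2[1 − Φ(1.96/f)]. For α = 0.05:

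- m = 25: f = √2.25 = 1.50, error rate 19%.
- m = 50: f = √3.5 = 1.87, error rate 29%.

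Simulation: 4,000 null trials per setting, 380 per arm, zero-inflated negative binomial data, zip count-part test. Ranges cover both zero shares and both readings of the mean:

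| α | Default SE: type I error |
|---|---|
| 0 (true zip) | 4.7-5.2% |
| 0.05 | 19-29% |
| 0.10 | 29-44% |
| 0.30 | 50-63% |
| 0.65 | 63-74% |

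Robust standard errors on the same simulated data gave about 4.6-6.0% at every dispersion tried. As a cross-check, 200 full maximum-likelihood zip fits (α = 0.65, 50% zeros, mean 50) gave an empirical SD of 0.091 against a mean model SE of 0.0146, and rejected in 68%.

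**The case against.** The strongest reply is that the article names a command, not a variance estimator. Robust standard errors are an option of zip itself, and an analysis plan not shown could call for them. A reader might infer that the primary p-value will be invalid whatever is done. The documents do not support that: the fault lies in zip with its default standard errors on overdispersed counts, and the robust option repairs it. What stands is that the published rule names a specific Poisson command and no safeguard.

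A second reply concerns the sample size. A reader might infer that 600 and 860 are wrong, or that the plan itself proves a dispersion near 0.65. Neither follows, because the article does not say which quantity was tested or what spread was assumed. If the difference in overall means was sized, with zero-inflated Poisson variance μ + μ²π/(1 − π), the totals are about 304-316 at 30% zeros and 672-700 at 50%. Using the control variance in both arms gives 368-381 and 816-848. The 848 is close to 860, but the same calculation gives 381 where 600 is stated. No variant tried gives both figures, so the count-part reading fits better but remains an inference.

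A reader might also object that zip can return two treatment coefficients and so creates two primary tests. The article does not say whether treatment enters the zero equation, and that detail may properly be left to the analysis plan.

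**Conclusion.** The concern holds as a conditional statement about a rule the article fixes. Zip with default standard errors keeps its 5% level only if days among patients with leave vary no more than a Poisson count. A variance 2 to 3.5 times the mean already gives about 19-29% false positives, and this does not depend on how the trial was sized. At the dispersion implied by sizing 600 and 860 on the count part, standard errors are about 4 to 6 times too small and type I error is about 60-73%. These larger figures are an illustration under that reading, not an established property of the trial. On the same reading, sizing and named analysis do not match (28-57 patients against 600-860).

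The results assume negative binomial spread, 380 patients per arm, and a test of the count coefficient with model-based standard errors.

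**What to change.** In the Statistical analyses section, replace zip with a zero-inflated or hurdle negative binomial model, or at the least specify zip with vce(robust). In the Sample size section, state the dispersion and the tested quantity behind 600 and 860. Preferably make the 12-month difference in mean sick leave days, combining both model parts, the single primary test, since the target effect is expressed on that scale.

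The cost is wording and one command, with no new data. The confidence interval becomes wider but valid.

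Power for the mean difference must be restated, because overdispersion adds to its variance. Take variance μ + μ²[(1 + α)/(1 − π) − 1], means 25 and 20, the same zero share in both arms and, as an assumption, α = 0.65:

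- 30% zeros: variances 873 and 563; total N = 2 × 7.849 × 1,436/25 ≈ 902.
- 50% zeros: variances 1,462.5 and 940; total N = 2 × 7.849 × 2,402.5/25 ≈ 1,509.

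The planned net number is 950 × 0.8 = 760. With α = 0 the same formula gives 304 and 672, so the answer depends heavily on the dispersion that the article should state.

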### Monitoring and data management

Before the start of recruitment, the neurological practices receive training on the interventions, use of the assessment instruments, the study documentation, the forwarding of the study documentation to the evaluating institutions, as well as the process and obligations regarding data validation. Online training is required, additionally, written and video-based training material is made available via the electronic health record platform and an access-restricted website.

Monitoring is carried out by the central project coordinator (BDN) and the evaluating institutions (UG and UMG). It starts directly after recruitment and the inclusion of the first patients. The principle of data Management has been described in a comprehensive data management plan.

## Discussion

To the best of our knowledge, this is the first study to consider multidisciplinary care in MS patients and its effects on health, gainful employment, and sick leave in Germany. In the project, patients with MS receive a bundle of interventions aiming to positively influence their ability to work and to participate in a self-determined life. The neurologist at the centre of the newly established network coordinates the care services offered by various service providers and, for the first time, works together with a preventive occupational physician. Tele-consultations and case discussions support this cooperation.

This complex intervention needs a highly integrated collaborative evaluation of health and health economic effects. In that way, primary and secondary data will be primarily matched, but due to the extensive collection of primary data within the project, a comprehensive evaluation of the new intervention is possible even in the absence of secondary data. The patient questionnaire and the documentation of MS-specific days of incapacity to work by the treating neurologists within the digital patient file make sufficient data available to analyze the primary endpoint, costs of incapacity to work and the course of treatment independently.

Complementing the patient perspective and the social and occupational participation outcomes achieved through the interventions, the perspective of service providers is also highlighted. Even though the new and comprehensive care for MS patients with the managing neurologist in the middle of the network can be understood as an innovation that goes beyond the current level of care. It is therefore of central importance that the new form of care is seen as useful and reasonable by the providers on the one hand, and that adequate financing can be ensured in the future on the other. The determination of the actual costs is thus indispensable for the transfer of this pilot implementation within the framework of MSnetWork.

Against this background, the study aims to improve the current employment situation of MS patients, considering disease-specific, therapeutic, psychosocial, and socioeconomic factors and the providers’ perspective to ensure such future treatment for MS patients.

If the project proves to be a success, a transfer for the treatment of other chronic diseases with an impact on the ability to work is conceivable and desirable.

## Data Availability

The study protocol is available as open access publication in agreement with SPIRIT [25] and CONSORT [26] criteria. The final trial dataset will primarily be available for the independent evaluation centres (UG and UMG) and the study coordinating centre (BDN). Data protection regulations restrict the use of the trial data for purposes and by institutions being agreed on by participants providing written informed consent. Any queries regarding data availability can be forwarded to the corresponding author. The trial results will be made available by scientific publication and reported to the funding body. Authorship eligibility guidelines for publishing peer-review journals will be applied.

## Abbreviations

9-HPT: 9-Hole Peg Test
AAQ: Adherence Assessment Questionnaire
BDN: Bundesverband Deutscher Neurologen (Professional Association of Neurologists)
CSE: Coping self-efficacy
CSES: Coping Self-Efficacy Scale
DASS: Depression, Anxiety and Stress Scale
EDSS: Expanded Disability Status Scale
EQ-5D-5L: EuroQol questionnaire, 5 dimensions, 5 level
FSMC: Fatigue Scale for Motor and Cognitive Functions
GWQ: Gesellschaft für Wirtschaftlichkeit und Qualität bei Krankenkassen (Society for Efficiency and Quality in Health Insurance Funds)
HRQoL: Health-related quality of life
ITT: Intention-to-treat
MS: Multiple sclerosis
MSFC: Multiple Sclerosis Functional Composite
MSQoL-54: Multiple Sclerosis Quality of Life-54 instrument
RCT: Randomized controlled trial
SDMT: Symbol Digit Modalities Test
SF-36: Short Form Health 36
SHI: Statutory Health Insurance
SPE-scale: Short scale measuring the subjective prognosis of gainful employment
T25-FW: Timed 25-Foot Walk
UG: University of Greifswald
UMG: University Medicine of Greifswald
VAS: Visual Analog Scale
ZUF-8: Patient Satisfaction Questionnaire
